#### Tertiary analysis

We will estimate the effect of the duloxetine regimen with full compliance using Complier Average Causal Effect analysis.^51^

#### Cost-effectiveness analysis

Two analyses will be conducted using the health system perspective: a cost-effectiveness analysis using the primary outcome as a measure of effectiveness and a cost-utility analysis where quality-adjusted life-years will be calculated using the EQ-5D-5L data collected at each follow-up. To obtain costs, administratively linked data will be used from the MBS for health services and the PBS for prescription medications. Participant questionnaires will identify the number of over-the-counter (OTC) medications and hospitalisations. OTC medications will be costed based on pharmacy websites and hospitalisations using the Independent Health and Aged Care Pricing Authority cost weights from the National Hospital Cost Data Collection. Bootstrapping will be used to calculate the confidence intervals around the incremental cost-effectiveness ratios. Sensitivity analyses will test uncertainty in key parameters such as the selection of cost weights.

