Anti-depressants are commonly used to treat chronic sciatica, but the evidence is inconclusive.^14 15^ In a 2021 systematic review, we found evidence suggesting that some anti-depressants, such as those from the serotonin-noradrenaline reuptake inhibitor (SNRI) class, may be effective for chronic sciatica and provide clinically worthwhile reductions in pain.^15^ However, estimates were based on three small (n=96), low-quality trials, and the certainty of evidence ranged from low to very low. Of the SNRI anti-depressants investigated for the management of sciatica, duloxetine appears to be the most promising. Duloxetine has been shown to be effective for the largest number of conditions among all other anti-depressants^14^ and is better tolerated than other anti-depressants commonly used for chronic pain conditions.^16^,^19^ Unlike opioids, duloxetine use has not been associated with the risk of misuse and addiction.^20^

Duloxetine is a potent inhibitor of serotonin and norepinephrine uptake, two key neurotransmitters involved in pain modulation.^21 22^ The analgesic effect of duloxetine has been attributed to both central and peripheral mechanisms based on research in animal models.^18^ These studies suggest a central mechanism that is rapid and requires descending noradrenergic inhibitory controls from the brain to the spinal cord plus a peripheral mechanism that is delayed and relies on the anti-neurogenic inflammation properties of duloxetine.^18^ The ability of duloxetine to reduce neurogenic inflammation makes it a promising pharmacological treatment for sciatica, a condition characterised by neuropathic pain.^23^ Duloxetine is also a low-cost treatment. For example, in 2024, the out-of-pocket cost in Australia for a 12 week treatment regimen of 60 mg per day followed by 2 weeks of tapering at a dose of 30 mg per day is estimated to be as low as $A91 (calculated based on dispensed price of 3×28 APO-Duloxetine 60 mg enteric capsules and 1×28 APO-Duloxetine 30 mg enteric capsules).^24 25^ Although not currently approved by the Therapeutic Goods Administration in Australia for the treatment of back pain, anti-depressants are commonly prescribed ‘off-label’ for back pain.^26^

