### Assignment of interventions: allocation/randomisation

An independent statistician not involved in any other aspect of the study will generate the randomisation sequence a priori using a computerised random number generator. Random allocation to either duloxetine or placebo will occur in a 1:1 ratio using randomly permuted blocks of various sizes. Study medication packs will be manufactured and labelled according to the randomisation sequence by the investigational medicinal product management company, Syntro Health. Medication packs will be allocated to the various recruitment settings (ie, general practice or specialist clinics, hospital or community) in complete block sizes. The study medication packs will be dispensed direct to the participant via a central pharmacy service provided by Syntro Health, except for those participants recruited from the hospital setting whose study medication will be dispensed via the hospital’s clinical trials pharmacy. The study medication packs will be dispensed sequentially from within the blocks allocated to the respective recruitment setting.

The participant will be enrolled into the study after the informed consent process has been completed and the participant has met all inclusion criteria, and none of the exclusion criteria and study medication has been prescribed for them. The participant will be dispensed a study medication pack with a unique study enrolment number. Randomisation will occur when the medication pack is allocated to the participant during dispensing.

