#### Study medication

Study participants will be provided with the blinded study medication pack containing either the active study medication (duloxetine 30 mg enteric-coated capsules) or matching placebo capsules manufactured and labelled to Good Manufacturing Practice standard by Syntro Health (Victoria, Australia).

Participants randomised to the active arm of the study will receive a 12-week course of oral duloxetine followed by a 2-week tapering phase. The starting dose will be duloxetine 30 mg/day for 1 week (one 30 mg capsule per day), increasing to 60 mg/day for 11 weeks (maintenance phase: two 30 mg capsules per day). In the 2-week tapering phase, they will receive 30 mg/day (one 30 mg capsule per day) for 2 weeks before treatment is discontinued.

The duloxetine regimen of 60 mg one time per day was chosen as it is the recommended dose for chronic pain and diabetic peripheral neuropathic pain.^30^ There is no evidence, including evidence from our review,^15^ that higher duloxetine doses (eg, 120 mg/day) confer additional benefits, but they do increase the incidence of adverse events and treatment discontinuation.^30^ The 12-week duration of the treatment is consistent with that reported in trials of duloxetine for other pain conditions.^14^ A 2-week tapering period is consistent with recommendations for the Australian population to minimise the risk of withdrawal symptoms.^20^

Participants randomised to the placebo arm of the study will receive the equivalent number of matching placebo capsules throughout the 14 weeks of the treatment phase.

Participants will be contacted by telephone at weeks 2, 6 and 12 by a blinded research team member to monitor treatment and collect adverse events data. This researcher, who will have nursing or pharmacy qualifications, may recommend participants to visit their study doctor for dose modification if they are experiencing troublesome adverse events or there are concerns regarding the participant’s safety. The responsible researchers will be trained and provided guidance regarding events and concerns that should receive medical attention. Study doctors, who also remain blinded, may make modifications to the treatment regimen if required. Changes and a justification for the changes will be noted in a treatment monitoring form. Participants will be allowed two follow-up visits to their study doctor during the active treatment phase, if required.

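### Bootstrap confidence intervals placed on the cost-effectiveness ratios can mix opposite conclusions; net monetary benefit should carry the uncertainty, and the costing of the study drug should be stated

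*Protocol article*

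**What the plan says.** The section on cost-effectiveness analysis in the protocol article plans a cost-effectiveness analysis on the primary outcome (leg pain) and a cost-utility analysis on QALYs from the EQ-5D-5L: "Two analyses will be conducted using the health system perspective". It fixes how uncertainty is expressed: "Bootstrapping will be used to calculate the confidence intervals around the incremental cost-effectiveness ratios". It names no cost-effectiveness plane, net benefit or acceptability curve. The sensitivity analyses are an open list: "Sensitivity analyses will test uncertainty in key parameters such as the selection of cost weights".

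On cost sources, the section says that "administratively linked data will be used from the MBS for health services and the PBS for prescription medications" and that "Participant questionnaires will identify the number of over-the-counter (OTC) medications and hospitalisations". The study drug reaches participants by another route. The section on allocation says that "The study medication packs will be dispensed direct to the participant via a central pharmacy service", with a hospital clinical trials pharmacy serving hospital recruits. The section on study medication describes trial-made packs of duloxetine or "matching placebo capsules manufactured and labelled to Good Manufacturing Practice standard by Syntro Health". The only price is in the Introduction, where the out-of-pocket cost of a course "is estimated to be as low as $A91".

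**The concern.** The choice of interval is stated in the text; it is not inferred from silence. A ratio of two differences does not order outcomes when either difference can change sign. A cost difference of +A$91 with an effect of −0.02 QALY gives −A$4,550 per QALY (dominated). A cost difference of −A$91 with +0.02 QALY also gives −A$4,550 (dominant). The order fails even within the dominant quadrant: −91/0.03 = −A$3,033 is the better result than −91/0.02 = −A$4,550, since the saving is equal and the gain larger, yet it ranks closer to zero. Percentile limits taken over such a set can join opposite conclusions in one interval.

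The design makes the case of a small or null effect relevant, because the trial has a futility boundary and may report with little or no difference. Cost-effectiveness is one of the stated secondary aims, and the reported interval is what a funder would read.

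The second question is whether the study drug enters the incremental cost at all, since none of the sources listed for costing would record a blinded pack made for and dispensed by the trial.

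**Working it through.** **The plan's own figure.** The economic section gives no figure, so the relevant one is the sample size, which sets the precision of the denominator. With a difference of 1, SD 2.5, two-sided 5% alpha and 90% power, n = 2 × (1.960 + 1.282)² × 2.5² / 1² ≈ 131.3, or 132 per arm. The t-test version gives 132.3, or 133 per arm (266 in total), as stated, with power 90.4% at 133. The group sequential maximum is 282 (141 per arm), and 282 / 0.85 = 331.8, or 332. These figures reproduce and are unaffected by this point.

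**Share of replicates with the wrong effect sign.** With SE = SD × √(2/n), the share is approximately Φ(−d/SE).

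*Leg pain*, 133 per arm: SE = 2.5 × √(2/133) = 0.307.

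| True difference (points) | d/SE | Share at or below zero |
|---|---|---|
| 1 | 3.26 | 0.06% |
| 0.5 | 1.63 | 5% |
| 0.25 | 0.82 | 21% |
| 0 | 0 | 50% |

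*QALYs*, 141 per arm. The article gives neither a QALY SD nor an expected gain; both are assumptions, shown as ranges.

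| Assumed gain | SD 0.10 | SD 0.15 | SD 0.20 | SD 0.25 |
|---|---|---|---|---|
| 0.01 | 20% | 29% | 34% | 37% |
| 0.02 | 5% | 13% | 20% | 25% |
| 0.03 | 1% | 5% | 10% | 16% |
| 0.05 | 0% | 0.3% | 2% | 5% |

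For example, SD 0.15 gives SE = 0.15 × √(2/141) = 0.0179, and Φ(−0.02/0.0179) = 13%.

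Early stopping raises these shares. At the article's expected total of 208 (104 per arm), a gain of 0.02 gives 7% to 28% over the same SDs.

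**What happens to the interval.** Ratios were simulated from 200,000 pairs of cost and effect differences with 133 per arm. The assumed inputs were a cost difference of A$91, cost SD A$1,000 and, for QALYs, SD 0.15.

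| Effect | Dearer, better | Dearer, worse | Cheaper, better | Cheaper, worse | 95% percentile limits of the ratio |
|---|---|---|---|---|---|
| QALY gain 0.02 | 66% | 11% | 20% | 3% | about −A$55,000 to +A$64,000 per QALY |
| Pain, 1 point | 77% | 0% | 23% | 0% | −A$171 to +A$453 per point |
| Pain, 0.25 point | 61% | 16% | 18% | 5% | −A$4,309 to +A$4,864 per point |

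In the QALY row, 11% + 20% = 31% of replicates are negative, and about a third of those (11/31) mean dominated, the rest dominant. At the 1-point pain effect all four quadrants are not in play: every negative value means dominant, and the interval can be read.

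**Drug cost, if omitted.** At A$91 per course, the incremental cost is too low by A$91. That is 91/1 = A$91 per pain point at the design effect. Per QALY it is 91/0.01 = A$9,100, 91/0.02 = A$4,550 or 91/0.03 = A$3,033 at assumed gains. The A$91 cannot be recomputed, because unit prices are not given. It is a lowest patient price, built mainly on 60 mg capsules while the trial supplies 30 mg capsules, so the health-system cost may differ.

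**The case against.** The best defence is that bootstrapping pairs of costs and effects yields the plane, net benefit and acceptability curve as by-products, that the article does not exclude them, and that displays are commonly left to a health-economic plan. This stands in part: nothing prevents the better summaries. But the article does name its summary, and the one it names is the one that fails.

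A second defence is that the leg-pain ratio is stable at the design effect, with 0.06% of replicates on the wrong side. That is correct. A reader might infer that both ratios are uninterpretable, or useless for any funding decision; the figures do not support that. The difficulty lies with QALYs at small gains, and with pain if the effect is well below 1 point.

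On drug cost, a reader might infer that the analysis is biased towards duloxetine. The article does not support this. It nowhere says that the study drug is excluded or costed at zero, and pricing the intervention is a detail that a condensed article may leave out. The quantities exist: the sections on study medication and outcomes describe intake diaries and counts of returned capsules. The outcomes section also has questionnaires covering prescription medicines, although a blinded pack would not yield a duloxetine cost there. Only the conditional statement survives.

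A reader might also see a contradiction between the health-system perspective and the costing of over-the-counter medicines. The article does not define whose payments that perspective covers, and no effect on a result can be shown, so this is at most a matter of labelling and is not pressed.

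**Conclusion.** The stated interval on the cost-effectiveness ratio is a poor choice and should be replaced. Its weakness is material for the cost-utility analysis: on assumed QALY SDs of 0.10 to 0.25 and 141 per arm, 5% to 25% of replicates have the wrong sign at a gain of 0.02 and 20% to 37% at 0.01, falling to 5% or less at 0.05. For leg pain it is negligible at the 1-point design effect and serious at 0.25 point or below. The QALY SDs, QALY gains and cost SD are assumptions; the pain SD and sample sizes are the article's own.

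The drug-cost point is secondary and conditional. If only the sources listed in the cost-effectiveness section are used, incremental cost is understated in duloxetine's favour, by about A$91 per course at the article's only price. Neither point touches the primary efficacy analysis or the safety analysis.

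**What to change.** Replace the sentence on intervals around the ratios. From the same bootstrap of cost and effect pairs, report:

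- incremental cost and incremental effect, each with a 95% confidence interval;
- the cost-effectiveness plane;
- incremental net monetary benefit, λ × ΔE − ΔC, with a 95% confidence interval at stated thresholds λ per QALY and per pain point;
- an acceptability curve;
- the ratio as a point estimate only.

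Net benefit is linear in both differences, so it stays ordered whatever their signs.

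Add one sentence saying that the study drug is costed in the duloxetine arm at a named public dispensed price, and whether this applies to capsules supplied or capsules taken.

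The cost is wording, a little more programming and a decision on thresholds before the analysis. No new data are needed.

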### Data monitoring

An independent Data Safety Monitoring Board (DSMB) will be appointed by the Steering Committee. The primary objective of the DSMB is to review unblinded safety (adverse event and serious adverse events) data and advise the DREAM Steering Committee Chair if any change to the study is recommended. The DSMB will also review data from the pre-planned interim analyses and recommend whether the trial should be stopped early according to the pre-specified group sequential design.

### Harms

Adverse events (AEs) and serious AEs (SAEs), both defined below, will be assessed at weeks 4, 8, 12 and 16 by self-report in the follow-up questionnaires and at weeks 2, 6 and 12 via direct questioning using the 21-item Antidepressant Side-effect Checklist.

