### Outcomes

The outcomes for this study were informed by a core set of outcomes recommended for back pain trials and consultation with consumers.^31 32^ Outcome measures, unless otherwise stated, will be collected by questionnaire at baseline, 4, 8, 12, 16, 26 and 52 weeks.

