Adverse events (defined under the Harms section) will be collected by self-report at weeks 4, 8, 12 and 16 via the online or phone follow-up questionnaires. Additionally, the research team will contact participants by phone at weeks 2, 6 and 12 to assess whether they have experienced any adverse events in general and in particular whether they have experienced any of those on the 21-item Antidepressant Side-Effect Checklist.^41^Work absenteeism will be measured in a questionnaire collected at all time-points. Participants will be asked to estimate the number of days off paid work in the period since the previous follow-up survey with the following question: ‘In the last 4 weeks (*or period since the last study follow-up*), did you miss any days off your normal paid work due to your sciatica?’.^42^Adherence to study medication will be measured by the participants’ self-report of daily medication intake, as recorded in an online or paper diary, and by comparing the count of returned medications against the doctor’s prescription.Healthcare use, including healthcare consultations, diagnostic and therapeutic procedures, imaging and pathology services, and prescription medicines, will be collected using administratively linked data from the Australian Medicare Benefits Schedule (MBS) and Pharmaceutical Benefits Scheme (PBS), respectively, and each follow-up questionnaire.

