#### Secondary analysis

The same model will be used to obtain estimates of the main effect of duloxetine at other time points for the primary outcome and for all time points for the secondary outcomes of a continuous nature. Adverse events will be classified, and the proportion of patients with adverse events and serious adverse events overall and within each category will be compared between groups using the Chi-square test.

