#### Adverse events

AEs are defined as any untoward medical occurrence in a participant administered the study medication. It does not necessarily have a causal relationship with the treatment.

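### The side-effect checklist has no baseline and none is listed after the week 12 call, so new complaints cannot be reliably separated from old ones and post-taper effects are not measured with the same instrument

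*Protocol article*

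**What the plan says.** Two sections of the protocol article give the same schedule. Harms states that adverse events are assessed "at weeks 2, 6 and 12 via direct questioning using the 21-item Antidepressant Side-effect Checklist". Secondary outcomes says "the research team will contact participants by phone at weeks 2, 6 and 12" and that these calls ask "whether they have experienced any adverse events in general and in particular whether they have experienced any of those on the 21-item Antidepressant Side-Effect Checklist". Separately, adverse events "will be collected by self-report at weeks 4, 8, 12 and 16 via the online or phone follow-up questionnaires".

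The Outcomes section sets a general rule: "Outcome measures, unless otherwise stated, will be collected by questionnaire at baseline, 4, 8, 12, 16, 26 and 52 weeks". Adverse events have their own stated schedule, so the baseline in that rule does not carry over to them.

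The definition under Adverse events reads "AEs are defined as any untoward medical occurrence in a participant administered the study medication", and the next sentence says that no causal link is needed. Under Secondary analysis, "the proportion of patients with adverse events and serious adverse events overall and within each category will be compared between groups using the Chi-square test".

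Tapering is planned to start at week 12, after the primary assessment, and to end at week 14. Its stated reason, under Study medication, is withdrawal: "A 2-week tapering period is consistent with recommendations for the Australian population to minimise the risk of withdrawal symptoms".

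**The concern.** Safety is one of the trial's stated aims, and the comparison is of proportions of patients with events. Part of the data comes from prompting people on a fixed list of 21 items. People with chronic pain, who may also take other analgesics during the trial, can plausibly have some of those complaints before the first capsule. Without a baseline on the same list, a complaint reported at week 2 may be new, worse or unchanged, and later analysis cannot reliably say which. An analysis plan can define what counts as treatment-emergent, but it cannot recreate data that were not collected. Where the article wants a baseline it says so: the depression, anxiety and sleep measures are each listed at baseline and week 8.

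The second gap is at the other end. Under the planned regimen the prompted instrument is last used just as tapering begins. Effects during treatment and effects of tapering and stopping are then recorded by different methods, which makes the two periods hard to compare.

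**Working it through.** **Schedule, set side by side**

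| Item | Weeks |
|---|---|
| 21-item checklist (phone) | 2, 6, 12 |
| Adverse event self-report (questionnaire) | 4, 8, 12, 16 |
| Planned taper | 12 to 14 |

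Checklists at baseline: 0. Checklists listed after week 12: 0. Adverse event questionnaires after the planned last dose: 1, at week 16.

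**Size of the baseline problem (illustration)**

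The article gives no adverse event rate to reproduce. The only input taken from it is the number per arm: the maximum of 282 in Sample size, divided by 2, is 141. (282/0.85 = 331.8, which rounds up to the stated 332.)

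Assumed, not from the article:
- A share b of each arm has the complaint before treatment, and all of it is reported.
- New onset occurs in 20% v 8% of those without the complaint.
- Worsening of an existing complaint is ignored.

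Formulas:
- Without a baseline, the proportion reporting is b + (1 − b)p.
- With a baseline, counting new complaints only, it is (1 − b)p.
- The difference is (1 − b)(p1 − p0) in both cases.
- Power = Φ[(d − 1.96·SE0)/SE1], where SE0 uses the pooled proportion and SE1 the separate proportions, two-sided 5%.

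Worked for b = 30%:
- Without a baseline: 0.30 + 0.70 × 0.20 = 0.440 and 0.30 + 0.70 × 0.08 = 0.356, so d = 0.084. SE0 = √(0.398 × 0.602 × 2/141) = 0.0583. SE1 = √((0.440 × 0.560 + 0.356 × 0.644)/141) = 0.0581. Power = Φ(−0.52) = 30%.
- With a baseline: 0.70 × 0.20 = 0.140 and 0.70 × 0.08 = 0.056, so d = 0.084 again. SE0 = √(0.098 × 0.902 × 2/141) = 0.0354. SE1 = √((0.140 × 0.860 + 0.056 × 0.944)/141) = 0.0351. Power = Φ(0.42) = 66%.

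| Background b | Difference, points | Risk ratio without baseline | Power without baseline | Risk ratio with baseline | Power with baseline |
|---|---|---|---|---|---|
| 0% | 12.0 | 2.50 | 83% | 2.50 | 83% |
| 10% | 10.8 | 1.63 | 58% | 2.50 | 78% |
| 30% | 8.4 | 1.24 | 30% | 2.50 | 66% |
| 50% | 6.0 | 1.11 | 17% | 2.50 | 51% |

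Reading down the table, the difference falls because fewer people are left who can newly develop the complaint. A baseline checklist does not undo that. Reading across a row shows what the baseline buys: the same difference with a smaller standard error, and a risk ratio that is not diluted.

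With 25% v 10% new onset instead, power without a baseline is 92%, 74%, 43% and 25% at the same four background levels.

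**The case against.** The strongest reply is that this is a preference about measurement and not an error. Adverse events are collected on seven scheduled occasions from week 2 to week 16 (two of them at week 12), against a blinded placebo, with an independent board reviewing unblinded safety data. Randomisation makes background complaints equally likely in both arms. The callers have nursing or pharmacy training and could ask about onset. Coding rules normally sit in the full protocol or the analysis plan. The trial is not powered on any adverse event, and every rate in the illustration is assumed.

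Much of this stands, and it rules out three stronger readings:

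- A reader might infer that withdrawal effects are not asked about. The week-16 self-report falls two weeks after the planned last dose and can capture them. Study doctor consultations are possible up to week 14, and participants who taper early after recovery may receive a checklist call during or after their taper. What is missing after the planned taper is the checklist. The article does not give the item format of the questionnaire, so its sensitivity is unknown.
- A reader might infer that pre-existing complaints are scored as adverse events. No section says so. The definition merely fails to exclude them.
- A reader might infer a bias toward finding no harm. The working does not show that: at any given background level the risk difference is the same with and without a baseline, and neither arm is favoured.

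Whether the Chi-square tests are accompanied by interval estimates is ordinary analysis plan content and forms no part of this point.

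The reply does not remove the schedule itself. The article states it twice, and neither coding rules nor an analysis plan can supply a baseline afterwards. Asking about onset at week 2 relies on recall and is a weaker substitute.

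**Conclusion.** The point holds as a cheap improvement to how safety is measured. The checklist has no stated baseline and none is listed after week 12. New complaints on it therefore cannot be reliably separated from old ones, and on-treatment and post-taper effects are not measured with the same instrument.

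If background complaints do enter the counts, the loss is in precision and in the risk ratio. In the illustration it is nil with no background and grows with prevalence: at 30% background, power is 30% without a baseline against 66% with one. These figures rest on the assumed onset rates, on full reporting of background complaints, and on 141 per arm. They show direction and order of size only. They are not an estimate for this trial, and the primary outcome is not affected.

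**What to change.** - Add the same 21-item checklist to the baseline questionnaire, completed before the first capsule, and to the existing week-16 survey. Keep the wording the same as in the calls, and record whether it was completed online or by phone, since the mode may differ from the week 2, 6 and 12 calls.
- State that a checklist item counts as an adverse event only if it is new or worse than at baseline.
- Summarise adverse events separately for the period on treatment and the period from the start of tapering, using each participant's own taper start where it was early.

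The cost is two extra completions of a short list in surveys already scheduled, a few minutes each, plus a small amendment and matching analysis plan wording. No new visit is needed and treatment does not change. Recruitment is planned from December 2024 to June 2027, so participants already enrolled would lack a baseline. Handle them in a sensitivity analysis, for example by comparing results with and without them, with the rule fixed before unblinding. The benefit is larger the earlier the change is made.
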